## Abstract

**Background:**

Adhesive capsulitis (AC) is a disabling and poorly understood pathological condition of the shoulder joint. The current study aims to increase our understanding of the pathogenesis, diagnosis and clinical outcomes of people with AC by investigating: 1) transcriptome-wide alterations in gene expression of the glenohumeral joint capsule in people with AC compared to people with non-inflammatory shoulder instability (controls); 2) serum and urine biomarkers to better understand diagnosis and staging of AC; and 3) clinical outcomes in people with AC compared to controls 12-months following arthroscopic capsular release or labral repair respectively.

**Methods:**

The study is a prospective multi-centre longitudinal study investigating people undergoing arthroscopic capsulotomy for AC compared to people undergoing arthroscopic stabilization for shoulder instability. Tissue samples collected from the anterior glenohumeral joint capsule during surgery will undergo RNA-seq to determine differences in gene expression between the study groups. Gene Set Enrichment Analysis will be used to further understand the pathogenesis of AC as well as guide serum and urine biomarker analysis. Clinical outcomes regarding pain, function and quality of life will be assessed using the Oxford Shoulder Score, Oxford Shoulder Instability Score, Quick DASH, American Shoulder and Elbow Society Score, EQ-5D-5 L and active shoulder range of movement. Clinical outcomes will be collected pre-operatively and 12-months post-operatively and study groups will be compared for statistically significant differences using linear regression, adjusting for baseline demographic variables.

**Discussion:**

This study will provide much needed information regarding the pathogenesis, diagnosis and staging of AC. It will evaluate clinical outcomes for people undergoing arthroscopic release of AC by comparing this group to people undergoing arthroscopic surgery for shoulder instability.

**Trial registration:**

ACTRN12618000431224, retrospectively registered 26 March 2018.

## Background

Adhesive capsulitis (AC), or ‘frozen shoulder’ is a debilitating pathological condition of the glenohumeral joint, characterised by stiffness, pain and dysfunction [1, 2]. The condition is estimated to affect 2–5% of the general population, most commonly in women and people aged 40 to 60 years [3, 4]. The natural history of AC has been described as self-limiting, with resolution of symptoms within 2 years [5]. However, many people experience prolonged symptoms and functional limitations [6]. Hand et al. [7] found that 41% of 223 patients reported ongoing symptoms at 4 years following symptoms onset, with 6% still reporting severe pain and functional loss.

Diagnosing AC is usually based on clinical findings [6]. The American Shoulder and Elbow Surgeons consensus definition describes AC as “functional restriction of both active and passive shoulder motion for which radiographs of the glenohumeral joint are essentially unremarkable except for the possible presence of osteopenia or calcific tendonitis” [8]. However, in the absence of objective criteria, particularly in the early-stage AC [9], diagnosis can be contentious [10]. Patients usually report the onset of shoulder pain before loss of motion [11, 12]. External rotation is often the first reported movement restriction [1, 13], which is thought to be consequential to contraction of the coracohumeral ligament, one of the essential diagnostic findings in AC [1]. X-rays can be used to rule out other causes of shoulder pain and stiffness [14]. Ultrasound, magnetic resonance imaging (MRI) and magnetic resonance arthrography can detect features suggestive of AC such as capsular thickening, and loss of the inferior axillary pouch and joint volume [14]. Blood tests are usually normal, though cholesterol, triglycerides and C-reactive protein might be elevated in the early stages [10].

The major pathological features of AC are inflamed glenohumeral and subacromial synovium, and thickening and contracture of joint capsule, particularly the rotator interval and coracohumeral ligament [1]. Inflammatory and fibrogenic cells and mediators such cytokines, macrophages and mast cells are elevated in AC capsular tissues compared to controls [15–17]. Inflammatory processes might initiate fibroblast proliferation and fibrotic processes, producing an imbalance between extracellular matrix tissue degradation, remodelling and regeneration; this disequilibrium might lead to fibrosis [1, 18]. Fibroblasts might also transform into myofibroblasts and cause capsular contracture [19], but myofibroblasts, also found in Dupuytrens disease associated with AC [20], have not been found in all AC tissue samples [21]. Neoangiogenesis and neoinnervation also occur in AC; the latter process may explain why AC can be intensely painful [1].

Although the macroscopic and histological features of AC are well described, the underlying pathogenic processes are less understood [18, 22]. In primary idiopathic AC, the aetiology is uncertain [22]. In secondary AC, there may be a history of trauma or surgery, myocardial infarction, type I or type II diabetes mellitus, hypothyroidism, or Parkinson disease [22]. Arkikila et al. [23] found the incidence of AC in people with type I or type II diabetes was 10 and 22% respectively.

The transcriptional profile of AC has received little research attention [12]. Evidence suggest a genetic predisposition towards AC using family history and racial predilection as markers for genetic association [22]. Identification and functional analysis of changes in gene expression associated with AC might help understand its pathogenesis [24]. Cui et al. [24] used RNA-sequencing to investigate the pathogenesis of idiopathic AC by comparing five tissue samples from people with AC to two people with acromioclavicular dislocation patients. One-hundred and eighty-eight differentially expressed genes were identified which encode proteins such as matrix metalloproteinases and cytokines. Hagiwara et al. [21] compared tissue samples from 12 people with idiopathic AC shoulders to18 people with rotator cuff tears and found the expression of 44 genes were significantly different; these genes related to fibrosis, inflammation, chondrogenesis and angiogenesis. Increasing the statistical power for these analyses might reveal new insights in AC pathogenesis and identify new biomarkers for diagnosis and treatment.

### Study aims

The primary aim of the current study is to investigate gene expression alterations in people with primary and secondary AC compared to people with non-inflammatory shoulder instability (controls). Secondary aims are: 1) to interrogate gene expression data to identify potential serum and urine biomarkers that might assist in the early diagnosis and staging of AC; and 2) investigate clinical outcomes in people with AC compared to controls 12-months following arthroscopic capsular release or labral repair respectively.

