### Setting

The study will be conducted at two large regional health services in Victoria, Australia: University Hospital Geelong and St John of God Hospital Geelong.

All participants will be recruited by one of three fellowship trained orthopaedic surgeons (RP, KE, GB) who subspecialize in shoulder surgery. Participants will be undergoing elective arthroscopic shoulder surgery for either capsular release for AC or labral repair for shoulder instability. Similar to other studies [25], patients with shoulder instability undergoing arthroscopic stabilization were chosen as the control group; these patients, for whom tissue samples can be taken, are not thought to have primary disease affecting the shoulder capsule [26], but experience significant pain and functional limitations [27].

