### Biosamples

Urine and venous blood samples will be collected immediately before the operation and transported to the Geelong Centre for Emerging Infectious Diseases (GCEID) laboratory for aliquoting and storage in secure − 80 degrees Celsius freezers. Venous blood will undergo the following tests: full blood examination; renal, thyroid and liver function tests; random glucose level; and HbA1C.

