### Clinical outcomes

Patient reported outcome measures will be collected pre-operatively and 12-months post-operatively and include the Oxford Shoulder Score [32], Oxford Shoulder Instability Score [33], Disabilities of the Arm, Shoulder, and Hand Questionnaire Short Version (Quick DASH) [34], American Shoulder and Elbow Society Score [35], and the EQ-5D-5 L [36]. Standardised data collection will be overseen by the study’s research manager. Active range of movement of the affected shoulder will be assessed by the patient’s surgeon pre-operatively and 12-months postoperatively. To maximise follow up rates, assessment of 12-month outcomes will be aligned with the study centre’s registry research program which routinely collects 12-month postoperative data [37].

Outcome data will be summarised using means with standard deviations or medians with lower and upper quartiles if the data are skewed. Outcomes for AC and control participants will be compared pre-operatively and at 12 months using linear regression, adjusted for potential confounders such as age, employment status and dominant arm. Tests will be considered significant when *p* < 0.05. The limitations of comparing inherently different groups, for example with different pathology and treatment, will be recognised when interpreting the results.

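### The biomarker aim and the abstract speak of early diagnosis and staging, but the design as described can only nominate markers that separate established surgical AC from shoulder instability

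*Protocol article*

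**What the plan says.** **The claim.** Study aims gives as the first secondary aim to interrogate the expression data and "identify potential serum and urine biomarkers that might assist in the early diagnosis and staging of AC". The abstract's Background lists serum and urine biomarkers in softer terms, as a route to better understanding of diagnosis and staging. The abstract's Discussion has no such softening: "This study will provide much needed information regarding the pathogenesis, diagnosis and staging of AC".

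**Who enters.** Under Setting, "Participants will be undergoing elective arthroscopic shoulder surgery for either capsular release for AC or labral repair for shoulder instability". Eligibility criteria requires symptoms for more than 3 months. For the AC group it also requires active movement reduced by over 30% in every direction relative to the other shoulder, with external rotation at least halved. The comparison group has more than one documented dislocation and a labral tear on MRI.

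**What is sampled, and when.** Biosamples states: "Urine and venous blood samples will be collected immediately before the operation". At 12 months, Clinical outcomes describes questionnaires ("Patient reported outcome measures will be collected pre-operatively and 12-months post-operatively") and active movement of the affected shoulder. No second blood or urine sample is described.

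**How candidates are chosen.** RNA extraction and transcriptomics analysis picks genes that differ between AC and control tissue, screens them for secreted or exosome-exported products, and confirms them by PCR with a between-group t-test. Those that differ then guide the work on plasma and urine from the two groups. Stage is not defined anywhere. Symptom duration is listed under Demographic data and is not tied to any biomarker analysis.

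**The concern.** The Background places the diagnostic difficulty at one end of the disease: "in the absence of objective criteria, particularly in the early-stage AC [9], diagnosis can be contentious". It adds that "Patients usually report the onset of shoulder pain before loss of motion". A marker for early diagnosis would have to work in people whose restriction is still slight or doubtful, and against other conditions that could be mistaken for AC. A staging marker would have to vary with stage among people who have AC.

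The described contrast does neither. It sets clearly stiff shoulders awaiting capsular release against recurrently dislocating shoulders with a torn labrum, a distinction that needs no biomarker. The comparator is reasonable for the primary gene-expression aim, where the need is capsular tissue without primary capsular disease. The difficulty arises only when the same contrast is carried over to diagnosis and staging.

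What is at stake is the conclusion. A marker that differs between these groups could be reported as an early-diagnosis or staging marker because the published aim and abstract use those words, although nothing in the described data bears on either.

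**Working it through.** The plan has no figure on this point to reproduce, so the main check sets the claim against the design.

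| What the claim needs | What the article describes | Section |
|---|---|---|
| Participants with early or mild AC | Elective surgical patients with more than 30% loss in all directions and at least 50% loss of external rotation | Setting; Eligibility criteria |
| A comparator that poses diagnostic doubt | "patients with shoulder instability undergoing arthroscopic stabilization were chosen as the control group" | Setting |
| Change in a marker over time, or a spread of defined stages | One blood and urine sample; no definition of stage | Biosamples; whole article |
| A contrast by stage | Selection by AC versus control | RNA extraction and transcriptomics analysis |

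On early cases, the 3-month symptom rule excludes little by itself. The motion-loss thresholds, together with the restriction to surgical candidates, are what make early or mild disease unlikely.

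On staging, the only information available is the cross-sectional spread among AC patients. How much could that show?

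*Inputs.* n = 25 AC patients (Sample size). Two-sided alpha 0.05 and 80% power are assumed here; the article gives a 0.05 threshold without sidedness, and no power.

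*Correlation of one marker with symptom duration (Fisher z).*
- SE = 1/√(n − 3) = 1/√22 = 0.213.
- Smallest observed correlation giving p<0.05: z = 1.96 × 0.213 = 0.418, so r = tanh(0.418) ≈ 0.40.
- True correlation needed for 80% power: z = (1.96 + 0.84) × 0.213 ≈ 0.597, so r = tanh(0.597) ≈ 0.53.

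*Two assumed stages within AC (normal approximation).* The detectable difference is (1.96 + 0.84) × √(1/n₁ + 1/n₂) SD.
- AC versus control, 25 v 25: 2.80 × √(2/25) = 0.79 SD. Power for a 0.8 SD difference is 81%.
- Two stages within AC, 12 v 13: 2.80 × √(1/12 + 1/13) = 1.12 SD. Power for 0.8 SD is 52%.

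These figures are for one marker with no covariates and no multiplicity correction. False discovery rate control and covariate adjustment would raise the thresholds. The entry criteria narrow the range of motion loss, which tends to weaken any correlation with severity. Also, a gene that changes with stage but does not differ on average between AC and instability would not pass the selection step, so no later within-AC analysis of the selected candidates could recover it.

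**The case against.** A reader might infer something stronger: that the aim cannot be met at all, because eligibility admits no early-stage participant. The document does not support that.

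- The aim in Study aims is hedged. It looks for potential markers that might help, which is candidate discovery with early diagnosis and staging as the motivation. Starting from clear-cut cases and testing early disease later is a legitimate sequence.
- The Background gives the usual order of symptoms; it does not define early-stage AC. The consensus definition used for entry itself requires restricted motion, and symptom duration has no upper limit. A count of zero early cases would rest on a stage definition that the article does not contain. What can be said is that such cases are unlikely.
- This is a condensed article. It does not specify the plasma and urine analysis in detail, and a within-AC analysis may stand in a fuller document. Its absence here is therefore not the defect.

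All three points stand, and they limit the finding. They do not remove it. The hedge is missing from the abstract's Discussion, which is the statement most readers will see. No analysis plan can add the early cases, diagnostically relevant comparators or repeat samples that the described design lacks. An unpublished staging analysis could use only the spread within about 25 patients, with the power shown above.

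**Conclusion.** The wording of the biomarker aim and of the abstract goes beyond what the described design can show. The design can nominate candidate serum and urine markers that separate established AC requiring surgery from shoulder instability. It supplies no evidence that a candidate detects early disease or tracks stage.

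This concerns a secondary aim. The sample size, the primary aim and the primary gene-expression comparison are unaffected, and no trial figure changes. The conclusion rests on the text: the entry criteria, the single sampling time, the lack of a stage definition and the group-based selection. The correlation thresholds of about 0.40 and 0.53 are illustrative. They assume 25 usable AC samples, two-sided alpha 0.05, 80% power and a single unadjusted marker.

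**What to change.** 1. Reword the biomarker aim in the abstract's Background and in Study aims, and the matching claim in the abstract's Discussion, to: *candidate serum and urine markers that distinguish established AC requiring surgery from shoulder instability*. Name early diagnosis and staging as later steps that need other participants and samples.
2. Specify, before the candidate measurements are analysed, one exploratory within-AC analysis of each candidate against symptom duration (Demographic data). Preoperative active range of movement of the affected shoulder (Clinical outcomes) may be added as a second exposure. Use that measure and not loss relative to the other side: the side-to-side comparison is an eligibility check and is not clearly a recorded variable.
3. Control the false discovery rate across candidates, report estimates with confidence intervals, and label the results hypothesis-generating.

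The cost is a narrower claim and one analysis with low power. No new participants, visits or samples are needed. If the authors want to keep the wider claim, they would need a definition of stage with a planned contrast, and either participants with early AC and comparators that pose real diagnostic doubt, or repeat samples. That is a different and larger study.

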## Methods

### Study design

This prospective longitudinal multi-centre study investigates the pathophysiology and clinical status of people with AC compared to people with shoulder labral tears and associated instability. See Fig. 1 for an outline of the study.

**Fig. 1 Fig1:**
[figure not shown]
Study flow diagram

### Setting

The study will be conducted at two large regional health services in Victoria, Australia: University Hospital Geelong and St John of God Hospital Geelong.

All participants will be recruited by one of three fellowship trained orthopaedic surgeons (RP, KE, GB) who subspecialize in shoulder surgery. Participants will be undergoing elective arthroscopic shoulder surgery for either capsular release for AC or labral repair for shoulder instability. Similar to other studies [25], patients with shoulder instability undergoing arthroscopic stabilization were chosen as the control group; these patients, for whom tissue samples can be taken, are not thought to have primary disease affecting the shoulder capsule [26], but experience significant pain and functional limitations [27].

### Eligibility criteria

Eligible participants have the following characteristics:18 to 70 years of ageSymptoms > 3 monthsNormal x-rayNo evidence of arthropathy or full thickness rotator cuff tear on bloods and MRIMRI studies will be performed on minimum 1.5 T scanners using the sequences: axial T1-weighted, coronal oblique T2-weighted with and without fat saturation, axial and sagittal oblique proton density, and sagittal oblique T2 fat saturationAC group (diagnosis based on consensus definition [8])Primary or secondary ACLoss of shoulder active motion > 30% in all directions compared to unaffected side including at least 50% reduction in external rotationComparison groupGreater than one episode of glenohumeral instability, defined as documented dislocation with labral tear on MRINo episode of instability in eight weeks prior to surgery (to reduce the likelihood of acute post-traumatic inflammatory reaction in the shoulder capsule)Willing, able and mentally competent to provide informed consent (able to read and understand the Patient Information and Consent Form which is written in English language).

People who have the following characteristics are not eligible:Bilateral shoulder pain or reduced motion affecting daily livingPrior shoulder surgery

Consecutive patients who fulfill the eligibility criteria will be invited to participate by a study surgeon at the pre-operative assessment. Informed written consent will be obtained as appropriate. Participation in the study is voluntary; no financial incentives will be offered, and recruitment will occur over a 2-year period, commencing in 2016.

### Biosamples

Urine and venous blood samples will be collected immediately before the operation and transported to the Geelong Centre for Emerging Infectious Diseases (GCEID) laboratory for aliquoting and storage in secure − 80 degrees Celsius freezers. Venous blood will undergo the following tests: full blood examination; renal, thyroid and liver function tests; random glucose level; and HbA1C.

### Surgical procedures

One of three fellowship trained orthopaedic shoulder surgeons (RP, KE, GB) will conduct each surgical procedure.

All participants receive general anaesthetic and interscalene block, and will be placed in the beach chair or lateral position consistent with published guidelines [28]. During the arthroscopy, two punch biopsies the size of rice grain will be collected under direct arthroscopic vision from the anterior capsule and rotator interval. Tissue samples are immediately placed in a vial containing RNA*later*™ stabilization solution (ThermoFisher).

In the AC group, each participant’s shoulder will be accessed with three arthroscopic portals and saline arthroscopic fluid at room temperature inserted into the joint space. Biopsies will be taken and rotator interval release conducted via an incision of the anterior capsule with the radiofrequency probe in the 1.00 to 5.30 position. Range of motion will be compared to the unaffected shoulder and a limited posterior capsule release performed by reversing the arthroscopic view if ranges are not equal.

In the instability group, each participant’s shoulder will be evaluated under anesthetic to determine the stability pattern of the glenohumeral joint, with clinical findings considered alongside pre-operative MRI findings. The joint space will be accessed with arthroscopic portals and biopsies collected. The labral tear will be prepared with liberator probes and shaver, and capsulolabral reduction and fixation anteriorly +/− posteriorly will occur with anchors according to the injury pattern.

Postoperative care of all participants, irrespective of group allocation will be according to the study centres’ protocols and care pathways. All participants will stay in hospital overnight. AC group participants will commence physiotherapist-supervised stretching and active-assisted ranging exercises from day 1 post-surgery. Instability group participants will use an immobilizer sling for at least four weeks post-surgery and then commence a rehabilitation program to improve active shoulder stability. Rehabilitation will be monitored for at least three months postoperatively. Incremental increases to range of movement exercises, strengthening and functional restoration will be incorporated into each participant’s individualized program. For the instability group, return to sport will be allowed after six months, pending the participant’s recovery.

